### Trial time scale

Preliminary experience from the pilot institution suggests that approximately six participants per site can be enrolled in 1 year. With at least 16 sites anticipated to participate in the study, a 24-month accrual period would result in approximately 180 enrollees. This provides an adequate margin for the target sample size of 194 patients, assuming a dropout rate of 8%. Follow-up is a minimum of 24 months.

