**Methods/design:**

A prospective, open-label, multicenter randomized controlled trial will be conducted in patients with progressive or symptomatic unresectable NET liver metastases. Patients will be randomized to treatment with bland embolization, lipiodol chemoembolization, or drug-eluting microsphere chemoembolization, with 60 enrollees per arm. The primary endpoint will be hepatic progression-free survival (HPFS) following initial embolotherapy by RECIST criteria. The sample size is powered to detect an HR of 1.78 for HPFS following chemoembolization compared with bland embolization, which was estimated on the basis of existing retrospective studies. Secondary endpoints include overall progression-free survival, duration of symptom control, quality of life, rate of adverse events, and interval between embolotherapy cycles. Interim safety analyses will be performed at 10 and 30 patients per arm.

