### Statistical considerations

#### Sample size calculation

Based on available retrospective data, median HPFS following BE is estimated at 11 months and cTACE at 20 months [9], corresponding to an HR of approximately 1.8. The effect of cTACE and DEB-TACE is presumed to be equivalent. Assuming a two-sided type I error rate of 10%, 60 participants per arm will provide at least 92% power for the overall log-rank test and 87% power for pairwise tests.

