### Randomization

The study will enroll 180 patients, who will be randomized in a 1:1:1 ratio to the three treatment arms. Randomization will be performed centrally and stratified by institution, using blocks of randomly selected sizes (3, 6, or 9). Patients with symptomatic but not progressive liver disease will be monitored during the accrual phase to ensure balanced allocation between treatment arms, with adjustment as necessary.

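### The enrolment figures cannot be reconciled: about 180 enrollees are said to give a margin over a target of 194, and the protocol does not say whether 60 per arm is before or after the 8% dropout

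*Protocol article*

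**What the plan says.** All statements are in the protocol article.

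- Abstract, Methods/design: three arms "with 60 enrollees per arm".
- Randomization: "The study will enroll 180 patients, who will be randomized in a 1:1:1 ratio to the three treatment arms".
- Sample size calculation: "60 participants per arm will provide at least 92% power for the overall log-rank test and 87% power for pairwise tests". This assumes a two-sided type I error rate of 10%. Dropout is not mentioned there.
- Trial time scale: about six participants per site per year, at least 16 sites, and "a 24-month accrual period would result in approximately 180 enrollees". The next sentence reads: "This provides an adequate margin for the target sample size of 194 patients, assuming a dropout rate of 8" (per cent). Minimum follow-up is 24 months.

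So 180 appears as the planned enrolment, as the projected accrual and (as 3 x 60) as the basis of the power. The figure of 194 and the 8% dropout appear only in Trial time scale.

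**The concern.** A projected 180 cannot give a margin over a target of 194. The sentence runs the wrong way, and the error reaches beyond it. The figure of 194 looks like 180 inflated for dropout, which would make 180 the number wanted after dropout. Yet the abstract, the Randomization section and the accrual projection all give 180 as the number enrolled. It cannot be both if 8% are expected to drop out.

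Two things are at stake. First, the number to be randomised decides when accrual closes. The Trial status section says enrolment was still under way at submission, and the document supports two different end points, 180 and 194. Second, a reader cannot tell whether the quoted power already allows for dropout.

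**Working it through.** **1. Enrolment arithmetic** (inputs from Randomization and Trial time scale)

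- Margin claimed: 180 - 194 = -14.
- Source of 194: 180 x 1.08 = 194.4. The figure is reproduced as 180 inflated by 8%.
- Stated accrual: 16 sites x 6 per year x 2 years = 192.
- 180 enrolled with 8% lost: 180 x 0.92 = 165.6, or 55.2 per arm.
- 194 enrolled with 8% lost: 194 x 0.92 = 178.5, or 59.5 per arm.
- 192 enrolled with 8% lost: 192 x 0.92 = 176.6, or 58.9 per arm.

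**2. Power model**

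Inputs from the article: "median HPFS following BE is estimated at 11 months and cTACE at 20 months" (ratio 20/11 = 1.82); an HR of 1.78 in the abstract and the Hypothesis section; equal effect in the two chemoembolization arms; two-sided alpha 0.10.

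Assumptions, not in the article: exponential HPFS, uniform accrual over 24 months, analysis at month 48.

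Expected event proportions with no dropout at HR 1.78 are 0.886 for bland embolization (median 11) and 0.712 for each chemoembolization arm (median 11 x 1.78 = 19.58). With 60 per arm that is 53.2 and 42.7 events: 95.9 for a pair and 53.2 + 2 x 42.7 = 138.6 in all.

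- Pairwise power = Phi(sqrt(V) x ln HR - 1.645). V is D/4 (equal allocation, D = events in the pair) or d1 x d2/D (event-weighted).
- Overall power = P(noncentral chi-square, 2 df, exceeds 4.605). The noncentrality is T x (1/3)(2/3) x (ln HR)^2 (equal allocation, T = all events), or (ln HR)^2 x d1 x 2d2/T (event-weighted).

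Worked case, 60 per arm, HR 1.78, ln HR = 0.577:

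- Pairwise, equal allocation: sqrt(95.9/4) x 0.577 - 1.645 = 1.18, so power is 0.881.
- Overall, equal allocation: noncentrality 138.6 x 0.2222 x 0.3325 = 10.24, so power is 0.894. Event-weighted: noncentrality 10.90, power 0.911.

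**3. Results** (each range spans the two variance forms)

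| Scenario | HR | Overall | Pairwise |
|---|---|---|---|
| Stated | | at least 92% | 87% |
| 60 per arm, no dropout | 1.78 | 89.4-91.1% | 87.7-88.1% |
| 60 per arm, no dropout | 1.82 | 91.2-92.8% | 89.6-89.9% |
| 55.2 per arm (8% lost entirely) | 1.78 | 86.9-88.8% | 85.2-85.6% |
| 55.2 per arm (8% lost entirely) | 1.82 | 88.9-90.7% | 87.2-87.6% |
| 60 per arm, dropouts censored* | 1.78 | 88.1-89.9% | 86.4-86.8% |
| 60 per arm, dropouts censored* | 1.82 | 90.0-91.7% | 88.3-88.7% |

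*Exponential dropout of 8% per 24 months, an assumption.

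The stated 92% and 87% are reproduced to within about 2 points by 60 per arm with no dropout (pairwise at HR 1.78; overall at HR 1.82, or at HR 1.78 event-weighted). They therefore look like power before any loss.

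**4. Cost of dropout alone**, taken within the same model: 89.4 to 86.9 and 91.1 to 88.8 overall, and 88.1 to 85.6 pairwise, which is 2.3 to 2.5 points with complete loss at HR 1.78. With censoring: 89.4 to 88.1 and 91.1 to 89.9, about 1.2 to 1.3 points.

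**5. Sensitivity to the analysis date.** If every patient had 48 months of follow-up, 55.2 per arm at HR 1.82 would give 92.0-93.1% overall. If every patient had only 24 months, overall power at HR 1.78 would be 83.6-86.3% with 60 per arm and 80.7-83.6% with 55.2. The level moves with the date; the cost of complete loss stays at about 2 to 3 points.

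**The case against.** The best defence is that the two figures in Trial time scale are simply swapped. Read as roughly 192 to 194 accrued for a target of 180, the sentence nearly works: 58.9 to 59.5 per arm remain after dropout. At HR 1.78 overall power would then be 88.9-90.6% with 58.9 per arm, against 89.4-91.1% with 60, a loss of about half a point. This is plausible, and it removes the power question. It does not remove the contradiction, because the abstract and the Randomization section would then state the wrong enrolment.

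A reader might infer that the trial falls short of 60 evaluable patients per arm and is seriously underpowered. The article does not support that. It speaks of participants and enrollees and never says that 60 is a number after dropout; that reading is inferred from 180 x 1.08. In a time-to-event analysis dropouts contribute until they are censored, and the Data management and monitoring section promises reasonable efforts to obtain imaging results and survival after withdrawal. Complete loss is therefore the worst case. Part of the gap to the stated overall figure is also not due to dropout: at HR 1.78 the model gives at most 91.1% with no dropout at all.

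Three further points should not be added to this one. The primary analysis is a studentized range test judged at the 95th percentile, while the power is for log-rank tests at 10%. Any loss from that mismatch is a separate matter. Dividing by 0.92 gives 196 where multiplying by 1.08 gives 194; two patients are immaterial. And 192 against about 180 is weak as an error in its own right, since the inputs are given as approximate or as minimums.

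**Conclusion.** The contradiction is certain and rests on no assumption: 180 is called sufficient for 194, and the same 180 serves as the number enrolled and as the basis of the power. Whether the two figures are transposed cannot be settled from the article.

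The consequence for power is modest. If enrolment stops at 180, dropout costs about 1 to 2.5 points under the month-48 model. Overall log-rank power is 87-91% with complete loss and 88-92% with censoring, below the stated 92% or more. Pairwise power is 85-88% and 86-89% respectively, within 2 points of the stated 87%. The levels depend on the assumed analysis date, the exponential form and the choice between HR 1.78 and 1.82. The reason to correct the text is that the trial needs one accrual end point, not that it is badly underpowered.

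**What to change.** 1. State one number to be randomised, and use it in the abstract, Randomization and Trial time scale.
2. Say whether 60 per arm is before or after the 8% dropout.
3. Rewrite the margin sentence so that the projected accrual and the target stand in the right order, and bring the projection into line with its own inputs (16 x 6 x 2 = 192).
4. If enrolment stays at 180, restate the power with dropout allowed for, giving the assumed analysis date and how dropouts enter the calculation.

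Keeping 180 costs only wording and a stated power that is slightly lower. If about 194 was always intended, the abstract and the Randomization section must change and 14 more patients are needed than the 180 now stated. At 96 per year (8 per month), that is 14/8, or about 1.75 months of accrual. Neither choice alters the endpoint or the analysis.

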### Statistical analysis

Our analysis will be aimed at identifying any embolotherapy arm that is significantly inferior (or superior) to the others based on comparison of the primary outcome. Our null hypothesis assumes that the arms are equivalent, without preconceived ranking. The test will use a studentized range approach developed for phase II screening trials using survival data [26, 27]. We will estimate the survival hazard rate in each treatment arm and compute the range of log-hazard rates (largest minus smallest). We will then compare the observed range to the distribution of the range under the null hypothesis. If the observed range exceeds the 95th percentile of its null distribution, any group whose hazard rate differs by more than this critical value from the group with the lowest PFS hazard will be declared significantly worse.

For secondary outcomes including symptom relief interval, time to reembolization, overall PFS, and PFS for subsets of the study sample, we will estimate the survival distribution using the Kaplan-Meier method. Comparisons among groups will be performed using log-rank tests, and survival regression models will be developed to estimate treatment effects, adjusted for baseline variables that may affect treatment outcomes.

For continuous outcomes (e.g., quality of life and symptom scores), summary statistics (mean, SD, 95% CI) will be assessed for each of the study arms, and comparisons among arms will be performed using one-way analysis of variance and *t* tests. Regression models will be used to estimate treatment effects adjusted for baseline variables that may affect treatment outcome. Binary variables (e.g., biomarkers) will be tabulated by treatment arm and compared using the chi-square test. Logistic regression models will be used to estimate adjusted effects.

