#### Primary safety endpoint

According to the Society of Interventional Radiology quality improvement guidelines for embolization and chemoembolization, major hepatic complications (biloma, abscess, liver failure) occur following approximately 6% of procedures, and the performance threshold is set at 8% [25]. The overall rate of any complication is 10%, with a performance threshold of 15%. All arms will be monitored for serious adverse events (SAEs) exceeding published thresholds. SAEs are classified as any event that is fatal; life-threatening; requires or prolongs hospital stay; results in persistent or significant disability, congenital anomaly, or birth defect; or an important medical event. Adverse events will also be classified using Common Terminology Criteria for Adverse Events (CTCAE) grading. Liver function test elevations of CTCAE grade 3 or lower and any clinical symptoms attributable to postembolization syndrome will not be reported unless they meet a criterion. All toxicities/events at or above CTCAE grade 4 will be reported. SAEs will be reported to the study sponsor by telephone and study form within 24 hours of the event. Interim safety analyses will be performed by an independent safety monitoring committee, which is composed of three interventional oncologists from institutions not involved in the trial, following accrual of 10 and 30 patients in each arm. A 20% rate of SAEs at these interim analyses will result in closure of the corresponding treatment arm.

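### The primary range rule, as spelled out, uses one unscaled critical value for every arm; if the safety rule closes a TACE arm at 10 patients, little power remains to separate BE from cTACE

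*Protocol article*

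**What the plan says.** The Statistical analysis section introduces the primary test by name: "The test will use a studentized range approach developed for phase II screening trials using survival data". It then gives the steps. A hazard rate is estimated in each arm, and the analyst will "compute the range of log-hazard rates (largest minus smallest"). The decision follows in two parts: "If the observed range exceeds the 95th percentile of its null distribution", then "any group whose hazard rate differs by more than this critical value from the group with the lowest PFS hazard will be declared significantly worse". No standard error, event count or weighting appears in these steps.

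The Primary safety endpoint section provides for safety reviews "following accrual of 10 and 30 patients in each arm" and states: "A 20% rate of SAEs at these interim analyses will result in closure of the corresponding treatment arm".

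The Sample size calculation section assumes 60 patients in each of three arms, median HPFS of 11 months for BE and 20 months for cTACE, and equal effect of the two TACE techniques. The article does not say whether a closed arm stays in the range, or whether later patients go to the remaining arms.

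**The concern.** The variance of an estimated log-hazard is about one over the number of events. With 60 patients in every arm, all pairwise differences have about the same standard error, so one cut-off in log-hazard units serves them all. If an arm stops at 10 or 30 patients, differences that involve it become much noisier than the difference between the two full arms. A single cut-off wide enough for the noisy pairs is then too wide for the precise pair.

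That precise pair carries the main question. If DEB-TACE closes early, BE versus cTACE is the comparison with complete data, and the stated rule would judge it against a threshold set mainly by noise in the closed arm. The conflict is between two rules the article states, on a path it foresees.

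**Working it through.** **Inputs.** Sample size calculation: medians 11 and 20 months, so the log hazard ratio is ln(20/11) = 0.60; 60 per arm; two-sided 10%. Hypothesis: HR 1.78. Trial time scale: 24-month accrual, at least 24 months of follow-up, 8% dropout. Statistical analysis: 95th percentile of the null range, so 5%. Assumed: exponential HPFS, analysis at month 48, full arms stay at 60, closed-arm patients still followed.

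**The plan's own figures.** Without dropout, expected events per 60 patients are 53.2 (BE) and 42.3 (each TACE arm), so 95.5 for a pair. Pairwise log-rank power at two-sided 10%: ln(1.78) × √(95.5/4) − 1.645 = 0.577 × 4.886 − 1.645 = 1.17, which gives 88% (stated: 87%). The overall test gives 91% at HR 1.78 and 93% at HR 1.82 (stated: at least 92%). The design assumptions reproduce.

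**Why one cut-off fails with unequal arms.** With 8% dropout and a common median of 15 months, mean events are 46/46/46 with no closure, 46/46/24 after closure at 30, and 46/46/8 after closure at 10. The 5% studentized range point for three groups is q = 3.31, and 3.31/√2 = 2.34.
- Two full arms: SE = √(1/46 + 1/46) = 0.209; suitable cut-off 2.34 × 0.209 = 0.49.
- Full arm against one closed at 30: SE = √(1/46 + 1/24) = 0.252; 2.34 × 0.252 = 0.59.
- Full arm against one closed at 10: SE = √(1/46 + 1/8) = 0.383; 2.34 × 0.383 = 0.90.

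**Simulation of the stated rule.** 200,000 trials per scenario, log-hazard = ln(events/person-months), true medians BE 11, cTACE 20, DEB-TACE 20. DEB-TACE is the closed arm, and the cut-off is rebuilt for the actual sizes at a common median of 14.5 months.

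| Arm sizes | Cut-off | BE exceeds cTACE by cut-off | BE declared worse than the lowest arm | BE v cTACE, pair-specific SE |
|---|---|---|---|---|
| 60/60/60 | 0.49 | 70% | 85% | 70% |
| 60/60/30 | 0.57 | 57% | 75% | 70% |
| 60/60/10 | 0.84 | 13% | 34% | 70% |

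Over null medians of 11 to 20 months, the 60/60/10 cut-off is 0.81-0.90 and the 13% ranges from 17% to 8%. The 70% starting point is below the stated 87% because the range test runs at 5%, allows for three comparisons, and dropout is included; that gap is not due to closure.

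**Check without dropout.** SE for BE v cTACE = √(1/53.2 + 1/42.3) = 0.206. Cut-offs at a null median of 15 months are 0.483, 0.556 and 0.822. (0.598 − 0.483)/0.206 = 0.56, (0.598 − 0.556)/0.206 = 0.20 and (0.598 − 0.822)/0.206 = −1.09, which give 71%, 58% and 14%. Simulation gives 72%, 59% and 15%.

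**Pair-specific test.** Simulated error under equality is 5.2% at 60/60/10 and 5.1% at 60/60/30.

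**How likely is closure?** Read the 20% as patients with an SAE, so that 2 of 10 or 6 of 30 closes an arm. At an assumed 10% SAE rate, one arm closes with probability 28% and at least one of three with 1 − (1 − 0.284)³ = 63%. At 5% the figures are 9% and 24%. If closure needed more than 20%, the chance per arm at the first look falls to 7% at a 10% rate.

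**The case against.** The strongest reply is that the section names a studentized method and cites its sources. Studentizing ordinarily means scaling by a standard error, and the sentences that follow are a summary. The cited method may handle unequal arms, and an analysis plan not shown may settle what happens to a closed arm. This stands in part: the text excludes neither pairwise scaling nor analysis of the completed arms alone, and either would avoid the problem. But the article goes beyond naming a method. It writes out a decision rule with one critical value in log-hazard units, and that rule, followed as written, performs poorly after early closure.

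Several stronger readings are tempting and should be resisted.
- A reader might infer that the test over-rejects. Error would reach 28-29% (closed at 10) or 10% (closed at 30) only if a cut-off computed for 60 per arm were kept. The text refers to the null distribution of the observed range, which is most naturally taken at the actual arm sizes.
- A reader might infer that any closure makes the designed difference undetectable. That does not hold at 30 patients, where the loss is moderate.
- With DEB-TACE closed at 10, in 73% of declarations against BE the small arm has a lower estimated hazard than cTACE. Those declarations are not false: BE is truly worse in that simulation.
- The closure probabilities are not predictions. The article gives neither an expected SAE rate nor the unit of the 20%, and its major-complication benchmark is per procedure.

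**Conclusion.** The concern holds in a limited form. The stated rule is sound for arms with similar information and poorly suited to the unequal arms that the safety rule can produce. The serious case is a TACE arm closed at 10 and kept in the range: the cut-off then exceeds the design effect, and BE-versus-cTACE power falls to about 13%. For closure at 30, a fall to about 57% is worth avoiding but is not a collapse. These figures rest on the assumptions listed in the working and on a null rebuilt for the actual sizes. The documents do not establish inflated error, because they do not prescribe the equal-arm cut-off after closure. The change should be made before any arm closes: choosing the scaling, and whether to keep the arm, after the fact in an open-label trial would leave the primary test open to question.

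**What to change.** In Statistical analysis, replace the common cut-off: divide each pairwise log-hazard difference by √(1/d_i + 1/d_j), with d the events per arm, refer it to the studentized range in Tukey-Kramer form, and declare an arm worse only on its own standardised difference. State in advance how an arm closed for safety enters the primary test. One option is to compare only the two continuing arms; at two-sided 5% that gives about 82% power with 60 in each, but the closed arm then gets no confirmatory efficacy verdict. Fix the significance level at the same time, since the range test uses the 95th percentile while the sample size section is written as "Assuming a two-sided type I error rate of 10"%.

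The cost is a few sentences, with no added patients or data and no change to the safety rule. With equal arms the test is practically the same as planned. The change does not recover information lost in the closed arm: if BE itself closes at 10, the chance of declaring it worse is about 36% with pair-specific scaling and 38% with the rebuilt common cut-off (no dropout).

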## Methods/design

### Hypothesis

The primary hypothesis of this study is that HPFS following TACE (lipiodol or DEB-TACE) will be nearly twice as durable as BE (HR, 1.78) for control of NET liver metastases. This will be tested against a null hypothesis of equality among embolization methods, without preconception of ranking.

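### The primary rule compares each arm only with the lowest-hazard arm, so it cannot conclude that bland embolization is worse than both TACE techniques

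*Protocol article*

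**What the plan says.** All references are to the protocol article.

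- **Statistical analysis, aim.** The primary analysis is directed at "identifying any embolotherapy arm that is significantly inferior (or superior) to the others based on comparison of the primary outcome".
- **Statistical analysis, statistic.** It will "compute the range of log-hazard rates (largest minus smallest") and compare that range with its null distribution.
- **Statistical analysis, decision.** Declarations follow only when the range passes its 5% cut-off. An arm is then judged by its distance from one reference: one that "differs by more than this critical value from the group with the lowest PFS hazard will be declared significantly worse". One cut-off serves both the overall test and the declarations. The log-rank comparisons later in the section concern secondary outcomes.
- **Hypothesis.** It expects that "HPFS following TACE (lipiodol or DEB-TACE) will be nearly twice as durable as BE (HR, 1.78"), tested against equality of the three methods.
- **Sample size calculation.** "Assuming a two-sided type I error rate of 10%, 60 participants per arm will provide at least 92% power for the overall log-rank test", with 87% for pairwise tests. The two TACE techniques are presumed equal in effect.

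**The concern.** Three arms form three pairs, and the rule examines at most two of them, both involving the arm with the lowest observed hazard. When a TACE arm is lowest, BE and the other TACE arm are never compared in the primary analysis. If the two TACE techniques truly perform alike, chance decides which one becomes BE's only comparator.

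The trial could therefore report BE as worse than the best arm, yet have no primary result for BE against the second technique. The hypothesis covers both techniques, and a pairwise power figure implies that each pair is a test of interest. When one TACE technique beats both other arms, the single cut-off also makes the second difference harder to declare than a step-down procedure would.

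**Working it through.** **Inputs from the protocol.** 60 per arm; HR 1.78 (Hypothesis); medians of 11 and 20 months, ratio 1.82 (Sample size calculation); 24 months' accrual and at least 24 months' follow-up (Trial time scale); 95th percentile of the range (Statistical analysis).

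**Assumptions.** Exponential HPFS, uniform accrual, analysis 24 months after the last entry, and each pair judged with its own standard error.

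**Step 1: expected events.** With λ = ln 2 / median, the event probability is 1 − [exp(−24λ) − exp(−48λ)] / (24λ).
- BE: λ = 0.0630, probability 0.886, 53.2 events of 60.
- Each TACE arm at HR 1.78 (median 11 × 1.78 = 19.58 months): λ = 0.0354, probability 0.712, 42.7 events of 60.

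**Step 2: reproduce the stated power (two-sided 10%).**
- SE of a pairwise log HR = √(1/53.2 + 1/42.7) = 0.2055.
- ln 1.78 / 0.2055 = 2.806, and Φ(2.806 − 1.645) = 0.877. The stated 87% for pairwise tests is reproduced.
- The overall 2-df test gives 0.894 to 0.911 at HR 1.78, and 0.912 to 0.928 at 20/11, against the stated 92%.

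**Step 3: the cut-off the rule applies.**
- The 95th percentile of the studentized range for three groups, divided by √2, is 2.344. This is a per-pair two-sided level of 1.9%.
- Observed HR needed: exp(2.344 × 0.2055) = 1.62. At 1.96 it is exp(1.96 × 0.2055) = 1.50.

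**Step 4: three procedures, simulated** (100,000 trials per scenario, HR 1.78, 60 per arm). All three start with the same range test at 5%. They differ in what follows: (A) the written rule; (B) all three pairs at 2.344; (C) closed testing, with all three pairs at 1.96.

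| Conclusion | A | B | C |
|---|---|---|---|
| Design scenario: BE worse than the lowest arm (A), or than a TACE arm | 83% | 83% | 83% |
| Design scenario: BE worse than both TACE arms | 0% | 54% | 68% |
| One TACE arm better: both others declared worse | 54% | 54% | 68% |
| False cTACE v DEB-TACE difference, design scenario | 1.9% | 1.9% | 4.8% |
| False difference between the two equal arms, one TACE arm better | 0.1% | 1.9% | 5.0% |
| Any false declaration, all arms equal | 5.0% | 5.0% | 5.0% |

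A normal approximation to the log-hazards, over HR 1.78 to 1.82, agrees. BE worse than both is 52–56% under B and 66–70% under C. With 8% of patients lost (55.2 per arm), the figures are 47–51% and 62–65%, and BE is flagged under A in 80–83%.

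**Step 5: why C holds 5%.** With three arms, equality of any two pairs implies equality of all three. The only joint hypothesis is therefore the global null, which the range test already tests at 5%. Once it is rejected, at most one pair can be truly equal, and that pair is tested at 5%.

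**The case against.** **The rule does what a screening rule sets out to do.** The section describes a method developed for phase II screening, with no ranking assumed beforehand. BE is flagged in about 83% of trials, and neither alternative raises that figure, because the range test is the same. This stands.

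**The hypothesis does not plainly promise proof against each technique.** Its parenthesis about lipiodol or DEB-TACE can be read as describing TACE in general. This stands in part. The pairwise power figure and the aim of finding an arm inferior or superior to the others still point to pairwise conclusions that the rule does not deliver.

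**Closed testing is not free.** This stands. A reader might infer that the rule gives up pairwise power with nothing gained in error control. That holds only for the maximum family-wise error. The written rule makes fewer false declarations when only some arms are equal, and the protocol presumes that the two TACE arms are.

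**A single-step cut-off is valid**, and it comes with simultaneous intervals that agree with its decisions. Unadjusted intervals could exclude 1 when the range test has not rejected. This stands and shapes the fix.

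**Unseen sources.** The cited method papers and any analysis plan are not at hand, and pairwise hazard ratios may be reported there. The article nevertheless states the primary decision rule in full, and that rule leaves one pair out.

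**Conclusion.** The concern holds as a cheap improvement, not as an invalid test. As written, once a TACE arm has the lowest hazard (over 99.9% of trials in the design scenario), the primary analysis cannot conclude that BE is worse than both techniques. Testing all pairs makes that conclusion available in about 54% of trials at the range cut-off, or about 68% with closed testing. Maximum family-wise error stays at about 5%.

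Two stronger inferences are not supported:
- **That BE has only about 42% power.** That figure is the 83% split by which TACE arm happens to be lowest, and the rule does not ask for a named arm.
- **That BE is never compared with the second TACE arm.** If BE were lowest, both TACE arms would be compared with it.

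The sizes rest on exponential HPFS, uniform accrual and HR 1.78. The 10% error rate in the sample size section conflicts with the 95th percentile in the analysis section. That is a separate point and part of the distance from the quoted 87%. At 10%, BE worse than both would be 65–68% with all pairs at the range cut-off and 78–81% with closed testing, and still 0% as written.

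**What to change.** Replace the last sentence of the primary rule so that, once the range test rejects at 5%, all three pairs are tested (BE v cTACE, BE v DEB-TACE, cTACE v DEB-TACE) and each conclusion names both arms.

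- **Minimum:** use the same range cut-off for every pair, with matching simultaneous intervals (log HR ± 2.344 × SE). The arms flagged are essentially unchanged, and the missing contrast is added. False declarations stay at 1.9% in the design scenario and rise from about 0.1% to 1.9% when one TACE arm is better.
- **Preferred:** closed testing for three arms, with each pair at unadjusted two-sided 5% and its own standard error. State the cost openly: false declarations between equal arms rise to about 5% in both scenarios. Label unadjusted confidence intervals as descriptive.

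Reconcile the 10% and 5% levels, then restate the power for the procedure adopted at that one level. The change needs one sentence in the analysis section and a revised power statement, with no further patients or data. It should be made before outcome data are compared by arm.
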